#### Neutralizing antibody titers

Neutralizing antibody titers to YF17D and JE-YF17D will be measured by plaque reduction neutralization test (PRNT) as described previously (16, 22). Briefly, 40 pfu of YF17D or JE-YF17D virus will be reacted with serial two-fold diluted serum samples and incubated at 37°C. This mixture will then be added to a monolayer of BHK cells and incubated for one hour before the addition of maintenance medium with carboxymethylcellulose. Back titration of virus will also be carried out to ensure that the amount of virus used is as indicated. The virus and cells will then be incubated for 3-5 days, following which, the cells will be washed, fixed and stained with crystal violet. The number of plaques will then be counted and PRNT_50_ titers estimated.

### Study discontinuation and withdrawal

Subjects are free to withdraw consent and discontinue their participation at any time without prejudice to them or effect on their medical care. Subjects may be withdrawn, if necessary, to protect their health or the integrity of the study. The investigator also has the right to withdraw participants from the study in the event of inter-current illness, adverse events, treatment failures, protocol violations, administrative, or other reasons. When a subject withdraws from the study, no new data will be collected for study purposes unless the data concern an adverse event related to the study. All details available will be reported and recorded for any subject that withdraws or is removed from the study. Subjects who drop-out or withdraw from the study will not be replaced.

The Principal Investigator (PI) may stop a subject’s participation in the study at any time for one or more of the following reasons: Failure to follow the instructions of the PI and/or study staff, the PI decides that continuing participation could be harmful to the subject, pregnancy, the study is cancelled, and/or other unanticipated circumstances.

## Data collection and management

### Data entry and storage

Direct data capture of demographic and clinical data will be conducted using computer notebooks. The data will be kept confidential in password protected computers accessible only by delegated research staff. Identifiers will be kept in a separate file in another office and every effort will be made to protect the privacy of the participants. The data to be analyzed will contain only de-identified data. An electronic data capture system (RedCap) will be used.

### Data quality assurance

The PI will review the study periodically for data and safety monitoring. Internal quality checks will be performed by two Clinical Research Coordinators (CRCs) who are study team members. The data entered by one CRC will be checked by another using the source documents. The study may also be evaluated by government inspectors/regulatory authorities who must be allowed access to the electronic data capture system (RedCap), source documents, and other study files. The inspectors will review CRFs and compare them with source documents to verify accurate and complete collection of data and confirm that the study is being conducted according to the protocol, ICH-Good Clinical Practices and all applicable regulations.

### Sample size calculation

To detect an effect size of 0.8 SD in mean RNAemia level on log (10) scale between the first and second dose with the same vaccine – first dose of YF17D will be analysed against those who received YF17D after JE-YF17D and vice versa – a sample size of 25 per group will provide 80% power at a 5% two-sided type 1 error rate. To allow for a drop-out rate of 10%, a total sample size of 28 per group for Arms 1 and 2 is targeted. For Arm 3, which is the control group, a sample size of 14 will be used.

### Data and statistical analysis

Distributional diagnostic plots will be used to examine the shape of distributions of T-cell counts and RNAemia levels for each of the vaccines. Parametric or non-parametric procedures will be used to assess the differences in RNAemia levels T-cell counts, antibody titers and cytokine levels, as appropriate. The peak frequencies of activated CD4+ and CD8+ T cells will be compared using the student’s t-test. The duration of activated CD4+ and CD8+ T cell responses will be compared using area the curve (AUC), and the differences will be assessed using the Wilcoxon-rank-sum test. The level of antigen-specific cytokine production will be compared within each vaccine. Overall kinetics of cytokine production will be assessed for each time-point and compared with the baseline levels using a paired t-test. The peak cytokine production and AUC will be compared between both vaccines using the student’s t-test or Wilcoxon-rank-sum test, depending on whether the distribution is parametric or non-parametric, using the Shapiro-Wilk normality test or equivalent. The relationship between the activated T-cell frequencies and cytokine levels will be assessed using Spearman’s correlation analysis. To compare differences in RNAemia, both peak RNAemia and AUC will be compared using the student’s t-test or Wilcoxon-rank-sum test, depending on whether the distribution is parametric or non-parametric, using the Shapiro-Wilk normality test or equivalent, respectively.

The frequency and type of adverse events reported will first be analysed by determining the median and the interquartile ranges. Differences in frequencies of adverse events between the first and challenge vaccination will be analysed using 2x2 tables and chi square analysis or Fisher’s exact test, whichever is appropriate. Parametric or non-parametric procedures will be used to assess the differences in pre-challenge virus-specific T-cell counts among those with adverse events and those without.

Linear regression analysis between peak RNAemia and T cell responses will performed to determine the minimal level of T-cell responses needed to reduce peak RNAemia by 1 log genome copies/ml. If, however, the correlation is non-linear (p > 0.05) a polynomial fit will be used to evaluate if a good model fit can be attained. Finally, in the unlikely event that none of these models fit the data points, the T-cell response for all subjects will be consolidated, and the T-cell responses that are at least 3 standard deviations away from the mean T-cell responses will be determined. These data points will be labelled as outlier responses, and the corresponding level of fold-change reduction in RNAemia will be determined. For all statistical comparisons, a p-value of <0.05 will be considered significant.

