### Study design

56 subjects will be randomized into 1 of 2 arms (Arm 1 and Arm 2) in a 1:1 ratio. These two arms will be double-blinded. Subjects in Arm 1 will receive JE-YF17D vaccine (IMOJEV^®^, Sanofi Pasteur) on Day 0, followed by YF17D vaccine (STAMARIL^®^, Sanofi Pasteur) on Day 28. Subjects in Arm 2 will receive YF17D vaccine on Day 0 followed by JE-YF17D vaccine on Day 28. A separate non-randomized non-blinded cohort of 14 subjects will be recruited into Arm 3. Subjects in Arm 3 will receive inactivated JEV vaccine (IXIARO^®^, Valneva) on Day 0 followed by YF17D vaccine on Day 28. **Table 1** summarizes the study design.

**Table 1 T1:** Study design.

Arms	Vaccination schedule	
	1^st^ vaccination (Day 0)	2^nd^ vaccination (Day 28)
Arm 1* (n=28)	JE-YF17D vaccine (IMOJEV^®^, Sanofi Pasteur)	YF17D vaccine (STAMARIL^®^, Sanofi Pasteur)
Arm 2* (n=28)	YF17D vaccine (STAMARIL^®^, Sanofi Pasteur)	JE-YF17D vaccine (IMOJEV^®^, Sanofi Pasteur)
Arm 3** (n=14)	Inactivated JEV vaccine (IXIARO^®^, Valneva)	YF17D vaccine (STAMARIL^®^, Sanofi Pasteur)

*Subjects (n=56) will be randomized in a double-blind manner to either Arms 1 or 2. **A separate cohort (n=14) will be recruited into Arm 3 in a non-randomized, single arm, open label design.

The rationale for these three study arms is as follows: Arm 1 will show the impact of a lower level of RNAemia induced by JE-YF17D vaccination (as compared to YF17D vaccination), and the resultant lower levels of virus-specific CD4+ and CD8+ T cells, would have on YF17D infection. In contrast, YF17D vaccination in Arm 2 would produce higher levels of RNAemia (as compared to JE-YF17D vaccination), and in turn higher levels of virus-specific T cells, thus likely resulting in greater suppression of JE-YF17D infection. The first vaccination in Arms 1 and 2 would provide the RNAemia response in the absence of virus-specific T cells, which would serve as a reference point to interpret the outcome of the second vaccination. For example, the level of suppression of JE-YF17D RNAemia will be the difference in RNAemia levels between subjects who received JE-YF17D as a second vaccination (Arm 2) compared to those who received it as a first vaccination (Arm 1), and similarly for YF17D vaccine. Arm 3 will serve as the control arm, as vaccination with inactivated JE vaccine should not produce any YF17D-specific T cell response.

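### Each virus contrast is tested on both peak and AUC of RNAemia at p<0.05 with neither named primary, and the sample size does not say which one it refers to

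*Protocol article*

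**What the plan says.** All references are to the protocol article.

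- **Primary objective.** RNAemia levels after the challenge vaccine are compared between the groups defined by primary vaccination, including the inactivated JEV group. No summary measure is named.
- **Sample size calculation, quantity.** "To detect an effect size of 0.8 SD in mean RNAemia level on log (10) scale", where the level is not specified as peak, AUC or a single day.
- **Sample size calculation, contrasts.** "first dose of YF17D will be analysed against those who received YF17D after JE-YF17D and vice versa". So two virus contrasts are named.
- **Sample size calculation, error and power.** "a sample size of 25 per group will provide 80% power at a 5% two-sided type 1 error rate".
- **Data and statistical analysis, summaries.** "To compare differences in RNAemia, both peak RNAemia and AUC will be compared", by t-test or rank-sum test.
- **Data and statistical analysis, decision threshold.** "For all statistical comparisons, a p-value of <0.05 will be considered significant".

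The same section uses peak RNAemia alone for the regression that seeks the T-cell threshold. Duration of RNAemia is a separate item under Secondary objectives.

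**The concern.** Two viruses times two summaries makes four p-values on the primary question, before any contrast with Arm 3. The article does not stay silent on how they will be judged. It fixes that both summaries are tested and that each is significant below 0.05. It does not say which summary answers the primary objective, or which one the sample size was computed for.

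At stake is how the main result is read. If peak and AUC disagree, or the two viruses disagree, the text gives no way to decide whether the primary hypothesis is supported, and that choice could be made after the data are seen. The 5% in the sample size section would then not describe the chance of a false primary claim.

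**Working it through.** **Step 1. The plan's own figure.** Inputs from Sample size calculation: difference 0.8 SD, two-sided alpha 0.05, power 80%, drop-out 10%.

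n per group = 2 × (1.960 + 0.842)² / 0.8² = 2 × 7.85 / 0.64 = 24.5, rounded up to 25. With drop-out: 25 / 0.90 = 27.8, rounded up to 28. Both stated figures reproduce. Power at 25 per group is 80.7% by the normal formula and 79.1% by the t-test. So the sizing is correct for one contrast on one summary, and it applies in turn to each virus.

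**Step 2. Error if the tests were independent.** Chance of at least one false positive = 1 − 0.95^k.

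- k = 2: 1 − 0.9025 = 9.75%
- k = 4: 1 − 0.8145 = 18.5%

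**Step 3. Error with correlation.** The tests are not independent. Peak and AUC come from the same samples, and both virus contrasts use the same subjects. The protocol gives neither correlation, so both are assumptions. The null case was simulated with 20,000 trials per setting, 25 per group, normal data and four two-sided t-tests. Rho is the peak-AUC correlation. Tau is the correlation between one subject's responses to the two viruses. Only the size of tau matters, because the tests are two-sided.

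| rho | tau 0 | tau 0.5 | tau 0.7 |
|---|---|---|---|
| 0 | 18.8% (exact 18.5%) | 17.3% | 16.3% |
| 0.5 | 17.5% | 16.2% | 14.8% |
| 0.7 | 16.2% | 14.6% | 13.8% |
| 0.9 | 13.7% | 12.7% | 11.7% |
| 0.95 | 12.6% | 11.4% | 10.4% |
| 0.99 | 11.4% | 10.2% | 9.4% |

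The range is about 9.4% to 18.5%. With one summary on both viruses it is about 8 to 10%. With one virus on both summaries it is about 5.6% (rho 0.99) to 9.75% (independent).

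**Step 4. What adjustment would cost** (t-test, 0.8 SD).

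- Unadjusted, alpha 0.05: power 79.1% at 25 per group, 83.6% at 28.
- Bonferroni over two viruses, alpha 0.025: 69.6% at 25, 75.2% at 28. For 80% power it needs 31 per group, or 35 with drop-out.
- Bonferroni over all four tests, alpha 0.0125: 59.4% at 25, 65.9% at 28. It needs 37 per group, or 42 with drop-out.
- Holm over two viruses: a contrast succeeds if its p is below 0.025, or if it is below 0.05 and the other is below 0.025. With independent contrasts and 0.8 SD in both, power per contrast at 25 is 0.696 + (0.791 − 0.696) × 0.696 = 0.762. At 28 it is 0.752 + (0.836 − 0.752) × 0.752 = 0.815. Whatever the correlation, at 25 it lies between 69.6% and 79.1%.
- Fixed sequence: power for the contrast tested second is about 0.791 × 0.791 = 0.63.

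**The case against.** The strongest reply has four parts.

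**The 5% is per comparison.** This stands. The sample size section names both virus contrasts, and its 5% is a valid rate for each. A reader might infer that the trial was sized for a single test; the words on the reverse comparison rule that out. Only the doubling into peak and AUC is absent from the sizing.

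**No rule says that any one of four positive tests counts as success.** This also stands. A reader might infer that the stated 5% is really about 14 to 18%. The documents do not support this, for two reasons. The familywise rate matters only if any positive test is read as success, and the protocol states no success rule either way. And 14 to 18% fits only peak-AUC correlations up to about 0.9. RNAemia is sampled only three times after each dose (Days 4, 7 and 10, then 32, 35 and 38), so a higher correlation and a lower figure are plausible.

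**AUC may be meant for the secondary duration objective.** It is the duration measure for T cells in the same section. For RNAemia, however, the text pairs AUC with peak to compare RNAemia in general and does not mention duration. If that was the intention, the primary family is two tests and the rate about 8 to 10%.

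**Ranking of endpoints and multiplicity belong in the analysis plan.** In general they do, and absence from a condensed article is no fault. Here the article itself fixes both summaries and a uniform threshold, and it sizes the trial on a quantity that it does not tie to either. That is open to criticism as written, even in an experimental study whose overall goal is a T-cell threshold.

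**Conclusion.** The point holds in a limited form. The sample size is arithmetically right and each test keeps its 5%. What is wrong is that the sized quantity is not identified, and that two summaries per virus are each tested at p<0.05 with neither named primary. If any positive result is taken as support for the primary hypothesis, the chance of at least one false positive is about 9 to 18.5%: 18.5% if all four tests are independent, towards 9% if both correlations are high. These figures assume normal data, 25 per group and correlations that the protocol does not report. Arm 3 contrasts, which the primary objective includes, are not counted and would add tests.

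This should be settled before analysis. It does not invalidate the design.

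**What to change.** 1. Name peak log10 RNAemia as the single primary summary; the threshold regression already uses it. State that the 0.8 SD and 25 per group refer to it.
2. Make RNAemia AUC supportive, reported with a confidence interval.
3. For the two virus contrasts, choose one of two statements in advance. Either 5% and 80% apply to each contrast separately and both are always reported, or Holm is applied across the two and power is restated: about 76% per contrast at 25 per group and about 82% if all 28 are evaluable, assuming independent contrasts.
4. Do not make the JE-YF17D test conditional on YF17D. The Study design section expects the greater suppression in the JE-YF17D challenge, so the contrast expected to be weaker would block the stronger one. Its power would fall to about 63%, below the 70% under plain Bonferroni.
5. Keep the Arm 3 contrast within the primary objective, where the protocol places it. Demoting it would change the objective, which is more than a change of wording.

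Cost: wording only and no added subjects. AUC alone could no longer support a primary claim, and power per contrast is slightly lower if Holm is chosen.

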## Safety assessment

### Definitions

An adverse event (AE) is any untoward medical occurrence in a patient or clinical investigation subject administered a pharmaceutical product and which does not necessarily have a causal relationship with this treatment. An AE can therefore be any unfavorable and unintended sign (including an abnormal laboratory finding), symptom, or disease temporally associated with the use of a medicinal (investigational) product, whether or not related to the medicinal (investigational) product.

A serious adverse event (SAE) is any untoward medical occurrence that at any dose results in death, is life-threatening, requires inpatient hospitalization or prolongation of existing hospitalization, results in persistent or significant disability/incapacity, or is a congenital anomaly/birth defect.

AEs will be graded according to the Common Terminology Criteria for Adverse Event Monitoring, version 5.0. Event terminology, the date and time of event start and end, severity, relatedness, impact to the continuation of the study, and final outcome of the event will be recorded on the case report form from day 0 to the last study visit until the event has been resolved. For a SAE, in addition to the above, an event summary, the criteria used to categorize the event as an SAE, and a list of all tests and treatments given for the event will be documented.

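### Median and interquartile range are set as the first summary of adverse event frequency and type; they are undefined for type and cannot separate an absent event from an uncommon one

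*Protocol article*

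**What the plan says.** The Protocol article deals with adverse event analysis in three sentences under Data and statistical analysis.

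- The descriptive step: "The frequency and type of adverse events reported will first be analysed by determining the median and the interquartile ranges".
- The comparison: "Differences in frequencies of adverse events between the first and challenge vaccination will be analysed using 2x2 tables and chi square analysis or Fisher’s exact" tests, whichever suits.
- A link to immunity: parametric or non-parametric comparison of "differences in pre-challenge virus-specific T-cell counts among those with adverse events and those without".

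Under Safety assessment, Definitions, the case report form takes "Event terminology, the date and time of event start and end, severity, relatedness, impact to the continuation of the study, and final outcome" of each event. Grading is fixed as well: "AEs will be graded according to the Common Terminology Criteria for Adverse Event Monitoring, version 5.0". Serious events get further documentation: "For a SAE, in addition to the above, an event summary, the criteria used to categorize the event as an SAE", plus the tests and treatments given. The section on serious adverse event reporting then sets out what goes to the ethics board and to the regulator.

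**The concern.** The descriptive sentence is a stated rule, not a detail left open, and it names a statistic that does not fit its object. Type has no order, so half of the sentence cannot be carried out. For the other half, a median of a sparse yes/no variable is zero for most individual symptoms, and so are both quartiles once fewer than about a quarter of subjects are affected.

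What is at stake is the plain description of which events occurred, in how many healthy volunteers, and how severe they were. The plan collects term, severity and relatedness for every event, yet the only stated analysis that refers to event type is this one. Secondary objective 6, on systemic symptoms after challenge, also concerns symptoms such as fever, myalgia, fatigue and headache. A reader would want those described one by one.

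**Working it through.** **Inputs.** Arms 1 and 2: "a total sample size of 28 per group for Arms 1 and 2 is targeted". Arm 3 has 14 subjects (Sample size calculation). The total is 28 + 28 + 14 = 70, which agrees with Study population. The figure of 28 reproduces as 25 / (1 - 0.10) = 27.8, rounded up. The plan gives no adverse event rate and no figure for the adverse event summary, so there is nothing further to reproduce.

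**Type.** A median needs ordered values. Fever, headache and myalgia have no order, so no median or quartile exists.

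**Frequency of one event term.** Assume one event per affected subject. With k of n subjects affected, the ordered data are n - k zeros followed by k ones. With linear-interpolation quartiles, the upper quartile lies at ordered position 1 + 0.75(n - 1). It is zero only if the next whole position at or above that point still holds a zero.

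- n = 28: position 1 + 0.75 × 27 = 21.25. The 22nd value must be 0, so 28 - k ≥ 22 and k ≤ 6.
- n = 14: position 1 + 0.75 × 13 = 10.75. The 11th value must be 0, so k ≤ 3.
- n = 70: position 1 + 0.75 × 69 = 52.75. The 53rd value must be 0, so k ≤ 17.

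The plan does not name a quantile definition, so five common ones were compared. The table gives the largest k for which the summary is 0 (0-0).

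| n | Linear, Hazen | Weibull, median-unbiased | Inverted CDF |
|---|---|---|---|
| 14 | 3 (21.4%) | 2 (14.3%) | 3 (21.4%) |
| 28 | 6 (21.4%) | 6 (21.4%) | 7 (25.0%) |
| 70 | 17 (24.3%) | 16 (22.9%) | 17 (24.3%) |

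The median alone is more forgiving still. At n = 28 it is the mean of the 14th and 15th values, so it stays 0 up to k = 13 (46.4%), or 14 under the inverted CDF. Just past the threshold the result is hard to read: 7 of 28 under linear interpolation gives 0 (0-0.25).

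**The same data as counts.** Events that all read 0 (0-0) become distinct. Exact 95% intervals are shown only to illustrate the precision.

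- 1/28 = 3.6% (0.1 to 18.3%)
- 3/28 = 10.7% (2.3 to 28.2%)
- 6/28 = 21.4% (8.3 to 41.0%)
- 1/70 = 1.4% (0.04 to 7.7%)

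**The case against.** The strongest reply is that this sentence is only the opening step. The 2x2 tables that follow consist of counts, and naming Fisher's exact test shows that sparse events were expected. A third analysis already divides subjects by whether they had an adverse event. This stands, and it limits the consequence. It does not repair the descriptive step, because the tables contrast first with challenge vaccination and are not stated to be by event type or grade. They are not stated to be pooled either; the text leaves this open.

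A second reply is that frequency may mean the total number of events per subject. Median (interquartile range) is then a defined and ordinary summary, and it reads 0 (0-0) only if fewer than about a quarter of subjects have any event at all. That also stands, and the documents give no event rate that would settle how likely this is. It rescues frequency on that reading, but not type.

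A reader might infer that uncommon or serious vaccine harms would vanish from the trial's safety results. The documents do not support that. Each serious event has its own summary, seriousness criteria and treatment record. Related serious events go to the ethics board, and unexpected related ones go to the regulator within set limits. These are documentation and reporting duties rather than a results table, but they mean that no serious event would be represented by a median alone.

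Finally, the article condenses a fuller protocol. Detailed table layouts may properly sit there or in an analysis plan, so their absence here is not a fault. The misapplied statistic is different, because it is written down.

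**Conclusion.** The point holds as a minor error in a stated analysis. The chosen statistic does not exist for event type. For an individual event term it cannot distinguish no events from events in up to 6 of 28 subjects (7 under one definition), 2 or 3 of 14, or 16 or 17 of 70. Saying that this covers events in under about a quarter of subjects is fair for the larger groups and slightly generous for Arm 3.

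The figures assume a separate yes/no variable per event term, one event per affected subject and full enrolment. They do not apply to total events per subject. The loss is limited to the descriptive summary by event type. The primary endpoint, sample size, data collection and serious event handling are untouched, and no clinical management rule is involved.

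**What to change.** Replace the descriptive sentence with one to this effect: *For each arm and each vaccination (first, challenge), the number and percentage of subjects with at least one adverse event will be given overall, by event term and by CTCAE grade. Median and interquartile range will be used only for the number of events per subject and for symptom duration.*

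A breakdown by relatedness, exact confidence intervals and an individual listing of serious events would be sensible, but they are optional layout choices that the full protocol or analysis plan can settle.

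The change is to wording only. Event term and severity are already recorded on the case report form, and symptom duration is already to be recorded, so no new data are needed. The cost is a slightly longer safety table.

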## Hypothesis and objectives

The overall goal of this study is to define a minimum quantitative threshold of T cells induced by vaccination needed to control subsequent infection, independent of antibodies. We will conduct an experimental study in healthy adult volunteers, leveraging on the immunogenic properties of the licensed live-attenuated yellow fever (YF17D; STAMARIL^®^, Sanofi Pasteur) and chimeric Japanese encephalitis-YF17D (JE-YF17D; IMOJEV^®^, Sanofi Pasteur) vaccines. These vaccines contain the same genomic YF17D backbone (13, 14): vaccination with either vaccine would likely produce T cell responses that, like other flaviviruses, are preferentially directed against the non-structural proteins encoded in their shared genomic backbone, and hence would cross-protect against each other (**Figure 1**). YF17D and JE-YF17D, however, encode different structural pre-membrane (prM) and envelope (E) proteins: vaccination with either would produce neutralizing antibodies protective only against that virus (15). Moreover, YF17D and JE-YF17D vaccination induce different levels of infection as determined by vaccine RNAemia (16, 17), and expectedly differing levels of innate immune responses, allowing us to evaluate how RNAemia and innate immune profile shapes T cell response. The properties of these two live-attenuated vaccines thus provide a unique opportunity to differentiate the role of T cell immunity from humoral immunity in controlling viral infection. In addition, we will also use the licensed inactivated Japanese Encephalitis virus (JEV; IXIARO^®^, Valneva) vaccine to control for the effects of cross-reactive anti-flaviviral antibodies, although we have not observed suppression of YF17D RNAemia from inactivated JEV vaccination (16). Overall, we hypothesize that a high CD4+ and CD8+ T cell response will reduce RNAemia upon challenge with a structurally heterologous virus, and correspondingly result in reduced magnitude of host response to challenge infection. The specific objectives of the study are as follows:

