#### T cell studies

The quantity of activated/proliferating T cells induced by vaccination will be assessed by measuring the frequency of activated effector CD4+ and CD8+ T cells expressing the activation markers CD38, and HLA-DR. The simultaneous expression of these two markers has been shown to accurately quantify the magnitude of T cell responses induced by live-attenuated viral vaccines (18, 19). Briefly, peripheral blood mononuclear cells (PBMCs) will be stained with a fixable live/dead marker and with antibodies specific to the surface markers CD3, CD4, CD8, HLA-DR and CD38. Stained cells will be fixed and then analysed by flow cytometry, as described previously (18).

The magnitude of YF17D-specific memory T cell responses induced by vaccination will be measured using three complementary methods: 1) Enzyme-linked immunospot assay (ELISpot), 2) Whole-blood cytokine release assay (CRA), and 3) Activation-induced Marker (AIM) assay. For all three assays, pools of 15-mer peptides overlapping by 10 amino-acids that span the C and NS1 to NS5 proteins of YF17D will be used to stimulate either PBMCs or whole blood *ex-vivo.* Overnight (16 hours) stimulation will be performed for the ELISpot assay (PBMCs) and CRA (whole blood), while a 24 hour stimulation will be performed for the AIM assay (PBMCs). ELISpot is a traditional assay which detects T cells that secrete IFN-γ in response to peptide stimulation. The whole-blood CRA measures the level of cytokines (e.g. INF- γ and IL-2) released by T cells in response to peptide stimulation and has shown good correlation with the ELISpot method (20). Finally, the AIM assay will be used to decipher whether the antigen-specific T cell response is sustained preferentially by CD4+ or CD8+ T cells – Briefly, PBMCs collected at various time points will stained with antibodies to the surface markers CD3, CD4, CD8 and activation markers CD134, CD137 and CD139. Stained cells will be fixed and then analysed by flow cytometry, as described previously (21).

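### The T-cell threshold regression names no deciding read-out and adds a second model try under an unadjusted p<0.05; with no true relation, a significant falling fit would arise in about 12–22% of trials under stated assumptions, against about 2.5% for one pre-named linear test

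*Protocol article*

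**What the plan says.** Hypothesis and objectives puts the threshold at the centre of the study: "The overall goal of this study is to define a minimum quantitative threshold of T cells induced by vaccination needed to control subsequent infection". It is not among the listed primary or secondary objectives. The primary objective compares RNAemia after challenge between vaccination groups.

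The analysis is in Data and statistical analysis: "Linear regression analysis between peak RNAemia and T cell responses will performed to determine the minimal level of T-cell responses needed to reduce peak RNAemia"; the target is a 1-log fall. The predictor is described only as T cell responses; no assay, visit or set of arms is given. A second step follows: "If, however, the correlation is non-linear (p > 0.05) a polynomial fit will be used to evaluate if a good model fit can be attained". A third step, an outlier rule at 3 standard deviations, applies "in the unlikely event that none of these models fit the data points, the T-cell response for all subjects will be consolidated". The section ends with a general rule: "For all statistical comparisons, a p-value of <0.05 will be considered significant". No adjustment is stated.

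T cell studies describes what could serve as predictor. One family comes from "measuring the frequency of activated effector CD4+ and CD8+ T cells expressing the activation markers CD38, and HLA-DR". For antigen-specific memory cells, "The magnitude of YF17D-specific memory T cell responses induced by vaccination will be measured using three complementary methods": ELISpot, whole-blood cytokine release and AIM.

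**The concern.** The plan sets out a route from data to threshold, but leaves the predictor open and permits more than one model per predictor, each under the same 5% rule. Each extra read-out and each extra model is another chance of a significant fit when nothing is there.

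A real relation does not remove the problem. Different assays can give different 1-log levels, in different units, and nothing says which one answers the study's question. If the best-fitting assay is the one reported, its slope will tend to be exaggerated, and the T-cell level needed for a 1-log fall will tend to be understated. The Discussion regards this information as foundational for choosing vaccine candidates, so a threshold set too low, or set by chance, would matter.

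**Working it through.** **Group size.** The article gives no error rate for the threshold regression, so the only stated figure to reproduce is the sample size. For 0.8 SD, 80% power and two-sided 5%: n = 2(1.96 + 0.84)²/0.8² = 24.5, so 25 per group. Power by the t distribution at 25 is 0.79, close to the stated 80%. With 10% dropout, 25/0.9 = 27.8, so 28. The plan's figures reproduce. They suggest about 25 evaluable subjects if one arm enters the regression and about 50 if Arms 1 and 2 are pooled; the plan does not say which.

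**Counting read-outs (T cell studies).**
- Activated CD4+ and CD8+ (CD38/HLA-DR): 2
- ELISpot: 1 ("ELISpot is a traditional assay which detects T cells that secrete IFN-γ in response to peptide stimulation")
- Whole-blood cytokine release, IFN-γ and IL-2, given as examples: 2
- AIM, CD4+ and CD8+: 2

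Total 2 + 1 + 2 + 2 = 7 at one visit. The schedule has T-cell sampling after the first dose and before challenge on Days 7, 10, 14 and 28 (pre-dose), so using several visits would add to this.

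**Simple benchmark.** Seven independent linear tests at 5%: 1 − 0.95⁷ = 30.2%.

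**Simulation with no true relation.** Normal outcome, independent of seven equally correlated normal read-outs; n = 25 to 50. Each read-out gets a two-sided linear test at 5%. If p>0.05, a quadratic is fitted and judged by its overall F test at 5%. A fit counts as falling if the linear slope is negative, or if the quadratic is lower at the highest T-cell value than at the lowest.

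| Assumed correlation | Linear only, any direction | Linear then quadratic, any direction | Linear then quadratic, falling |
|---|---|---|---|
| 0.3 | 26–29% | 39–41% | 20–22% |
| 0.5 | 23–24% | 34–36% | 17–19% |
| 0.8 | 14–16% | 23–26% | 12–14% |

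**Comparators.** One pre-named read-out with one linear fit: 5% in either direction, so about 2.5% falling. The second model try alone raises the either-direction rate for a single read-out to about 7–8%. Against 2.5%, the falling rate for seven read-outs is 12/2.5 = 4.8 to 22/2.5 = 8.8 times as high.

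**Sensitivity.**
- Four read-outs: falling fit in about 10–14%, or 10/2.5 = 4 to 14/2.5 = 5.6 times the comparator.
- Quadratic term tested alone, seven read-outs, either direction: 31–33% at correlation 0.8 and 50–52% at 0. The overall F test is the milder choice.
- Correlation 0.9, overall F test, either direction: 18–20%.
- Significant fit that also drops by at least 1 log within the observed range (seven read-outs, n = 28 to 70, correlation 0 to 0.8): 1–7% at an assumed RNAemia SD of 0.5 log, 11–24% at 1 log, 13–25% at 1.5 log. The article gives no SD on the log scale.

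The outlier rule is not in any of these figures.

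**The case against.** The strongest reply has four parts.

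*The larger percentage is not the chance of a false threshold.* A reader might infer that a threshold appears by chance in 23–41% of trials. The documents do not support that. The threshold is a level needed to reduce RNAemia, so a rising fit yields none, and counting only falling fits roughly halves the figure. The 1-log requirement can reduce it much further if the RNAemia SD is small. All these rates also hold only if no read-out is related to RNAemia. This part stands, and the conclusion rests on the smaller figure.

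*Seven predictors and a quadratic are not written.* The article does not say that every read-out enters the regression. It lists T-cell counts and cytokine levels separately, and it gives AIM the role of separating CD4+ from CD8+ responses. It gives no polynomial degree and asks only for a good model fit; p<0.05 for that step is inferred from the blanket rule. This also stands, so these are assumptions. With four read-outs the excess remains.

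*Naming the predictor and handling multiplicity may sit in an analysis plan that is not shown.* This is partly right: an unnamed predictor alone would be a weak point. But the article also writes a sequence of model tries and a universal unadjusted rule, which a later document would have to override.

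*The threshold is not a listed objective, and several read-outs may be intended.* The Introduction speaks of frequency and functionality, and the Discussion disclaims a universal correlate. No sentence says that whichever assay reaches p<0.05 will be declared the correlate. That reading goes too far; the fair statement is that nothing in the article prevents it.

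**Conclusion.** The point holds in a limited form. For the study's overall goal, the plan fixes a sequence of fits on an unnamed T-cell predictor under an unadjusted 5% rule. With no true relation, seven read-outs at one visit, a quadratic judged by overall F at p<0.05 and correlations of 0.3–0.8, at least one significant fit arises in about 23–41% of trials and at least one falling fit in about 12–22%, against about 2.5% for one pre-named linear test. With four read-outs the falling figure is about 10–14%. The 1-log requirement could bring the seven-read-out rate down to 1–7% if the RNAemia SD is 0.5 log, but hardly lowers it at 1 log or more.

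The correlations, the number of read-outs entered, the form and test of the polynomial, and the RNAemia SD are all assumptions. The primary RNAemia comparison is unaffected. The point does not depend on whether p>0.05 is a sound sign of non-linearity, which is a separate question.

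**What to change.** Before unblinding, the sponsor should:

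- name one deciding pre-challenge T-cell read-out and its visit for the 1-log threshold, or a small named set such as CD4+ and CD8+ with Holm adjustment (for two, the smaller p-value is compared with 0.05/2 = 0.025);
- state one functional form for that regression, in place of a second try triggered by the first p-value;
- report all other read-outs as supportive, with Holm or permutation max-T adjusted p-values across the set;
- give a confidence interval for the T-cell level, and claim a threshold only from the deciding read-out or set.

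Which assay decides is the sponsor's scientific choice. The hypothesis concerns both CD4+ and CD8+ responses, and the article assigns that separation to AIM rather than ELISpot, so a two-member set may suit it better than one pooled count.

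The cost is a few sentences, with no new samples or subjects. The downside is that a significant result in a non-deciding assay can be reported only as supportive.
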